### 2.5. Restrictions During Participation in the Trial

Participants will be instructed not to take other products containing probiotic bacteria, to fast overnight (water is allowed and encouraged) before visits, which require the collection of blood samples, and to refrain from hormone replacement therapy for the duration of the trial. Should a participant withdraw early from the trial, they will not be unblinded before the data analysis is complete. The participants will be requested to continue their normal physical activity and dietary patterns while in the trial.

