## Abstract

Background/Objectives: Correction of decreased diversity of the gut microbiome, which is characteristic of menopause, by supplementation with a synbiotic may attenuate or prevent dysbiosis processes and preserve bone mass. We describe the rationale and design of the OsteoPreP trial aimed at evaluating the effects of 12 months of supplementation with a synbiotic on bone and metabolic health in postmenopausal Caucasian women. Methods: This is a randomized, double-blinded, placebo-controlled trial among 160 Caucasian, postmenopausal women with no current diagnosis of osteoporosis or supplementation with pro- or prebiotics, and no medical treatment affecting bone turnover. Dual-energy X-ray absorptiometry scans will be conducted at screening to confirm absence of osteoporosis. The primary outcome is the relative change (%) in total bone mineral density of the distal tibia at 12 months post-treatment between the active and placebo groups, as determined via high-resolution peripheral quantitative computed tomography. Secondary outcomes are the effects on immune system modulation and cognition, gut microbiota composition, and musculoskeletal and metabolic functions, with particular emphasis on blood glucose regulation. Conclusions: The trial will inform on the efficacy and safety of a synbiotic containing both aerobic and anerobic bacterial strains and a prebiotic fiber on reduction in bone loss and on indices of blood glucose regulation. This trial may pave the way for an exciting field of translational research and be the underpinnings of the prevention strategy of osteoporosis and the management of metabolic dysfunction in postmenopausal women. The trial is registered with clinicaltrials.gov (NCT05348694).

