Given the critical role of probiotics in several processes central to osteoporosis prevention, a unique opportunity exists to examine the safety and efficacy of this relatively inexpensive, readily available, oral dietary supplement in a clinical trial focused on preventing osteoporosis. The trial intervention is a formulation of five probiotic strains important for the production of SCFA butyrate, which have previously been found to be beneficial to bone and metabolic health and neurodevelopmental disorders [62,63,64,65,66,67]. Additionally, the intervention contains a prebiotic, inulin, known to promote the growth of beneficial microbes and/or promote beneficial changes in the activity of the microbiome [68]. To our knowledge, this is the first randomized controlled trial to administer a mix of all five probiotic strains and a prebiotic in a supplement formulation (Pendulum WBF-038) to human subjects with a risk of developing osteoporosis, over a 12-month treatment period. If supplementation with the trial synbiotic is beneficial for bone health, cardiometabolic health, muscle health, and cognition, the results of this trial could translate into significant improvements in the prevention of osteoporosis and related musculoskeletal and metabolic conditions, such as T2DM [69].

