### 2.4. Interventions

All bacteria contained in the IP are commensal organisms that are known to inhabit the human gastrointestinal tract under normal conditions. Pendulum WBF-038 is a proprietary synbiotic formulation of five human-derived bacterial strains: *Akkermansia muciniphila* WB-STR-0001, *Anaerobutyricum* (formerly *Eubacterium*) *hallii* WB-STR-0008, *Clostridium butyricum* WB-STR-0006, *Clostridium beijerinckii* WB-STR-0005, and *Bifidobacterium infantis* Bi26TM, plus chicory inulin and magnesium stearate. The bacterial strains were grown in an FDA-registered food facility adhering to current good manufacturing practice conditions for food manufacturing facilities. Pendulum WBF-038 contains no genetically modified organisms, and its bacterial strains are generally recognized as safe.

The IP will be provided to the research team as acid-resistant capsules in identical bottles, which have been pre-coded by the supplier according to the randomization list and stored refrigerated at 4 °C. The participants received either Pendulum WBF-038 or matched placebo capsules containing only magnesium stearate. The daily dose in two capsules of WBF-038 is ≥2 × 10^9^ active fluorescent units. The dosage was determined in reference to a previous trial [71]. At T0, the participants will be dispensed IP along with calendars to record their adherence as well as a tip sheet on how to take the IP (Figures S1 and S2). The participants will be directed to take the assigned IP twice daily within 30 min of the morning and evening meals during phase 2 (treatment) of the trial. At six (T2), twelve (T4), and final (T5) visits, participants will be instructed to return the used IP containers (and any unconsumed IP), and compliance will be recorded. Compliance will be calculated based on returned capsules and the information recorded by participants on their IP calendars, with >80% compliance required for continuation in the study. The IP intake will be discussed at each visit to ensure compliance is tracking as per protocol. If a participant is unable to take the allocated IP because of an adverse event (AE), the researchers will alter the principal investigator according to internal guidelines.

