### 2.8. Sample Size

The sample size calculation was based on data from a previous probiotic intervention study in older women, which demonstrated a significant effect on bone health outcomes. For this study, additional metabolic outcomes are included, and effect sizes for these outcomes were estimated based on prior research using similar synbiotic interventions in comparable populations.

Permitting for possible participant attrition, the total sample size for the trial will be 160 (80 per arm), taking a 20–30% drop-out rate into account. Statistical power analysis will be performed in relation to the primary outcome of the relative twelve-month change (%) in total BMD using HR-pQCT at the distal tibia. On the basis of a similar probiotic intervention in older women [100], the expected decrease in tibia BMD is 1.85% in the placebo arm and 0.9% decline at most in the treatment arm, with a standard deviation (SD) of 1.6% and an alpha of 0.05; 46 participants are needed in each arm to achieve >80% power. To be able to detect smaller groups to group differences and to account for an attrition rate of 20–30% and due to many secondary outcomes, we will recruit a minimum of 80 participants into each arm.

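### Entry excludes users of probiotics or prebiotics, but the in-trial restriction names only probiotic products, although inulin is part of what the trial compares with placebo

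*Protocol article*

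**What the plan says.** Four places in the protocol article bear on this.

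- **Entry (Abstract).** The population is women with "no current diagnosis of osteoporosis or supplementation with pro- or prebiotics". Both classes of product are named.
- **During the trial (2.5, Restrictions During Participation in the Trial).** "Participants will be instructed not to take other products containing probiotic bacteria". Hormone replacement therapy is also ruled out there by name. Prebiotics, inulin and fibre supplements are not mentioned. The section closes with a general request: "The participants will be requested to continue their normal physical activity and dietary patterns while in the trial".
- **The products (2.4, Interventions).** The active capsule holds five bacterial strains "plus chicory inulin and magnesium stearate". The comparison arm receives "matched placebo capsules containing only magnesium stearate".
- **The role of inulin (1, Introduction).** Inulin is presented as contributing to the effect: "the intervention contains a prebiotic, inulin, known to promote the growth of beneficial microbes".

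Table 1 schedules a Current Medications record, by self-report and interview, at screening and at every visit from T0 to T5. It schedules dietary questionnaires at T0, T2 and T4. Section 2.9 plans intention-to-treat and per-protocol analyses; the article does not define the per-protocol population.

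**The concern.** The product is a synbiotic, so the randomized contrast is strains plus inulin against neither. The plan treats prior prebiotic use as important enough to define the population by its absence, and the same reasoning applies during the 12 months of treatment. Yet the rule for those months covers only products that contain bacteria. Inulin contains none, so the wording cannot be stretched to include it.

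If placebo women take up a prebiotic, they receive part of the tested product. On the plan's own premise that inulin helps, the placebo arm then loses less bone than assumed, and the difference shrinks. The same could happen to the microbiome, short-chain fatty acid and glucose outcomes, which lie closer to inulin's stated action than tibial bone density does. Section 2.8 recruits beyond the calculated need partly to detect smaller differences, and contamination would use up some of that margin.

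**Working it through.** **Step 1: the wording side by side**

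| Product class | Entry (Abstract) | During the trial (2.5) | In active product (2.4) | In placebo (2.4) |
|---|---|---|---|---|
| Probiotic | excluded | barred | yes | no |
| Prebiotic | excluded | not named | yes (inulin) | no |

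The second row is the mismatch. It follows from the text and needs no calculation. The rest only gauges its size.

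**Step 2: inputs from 2.8**

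- Means: "the expected decrease in tibia BMD is 1.85% in the placebo arm and 0.9% decline at most in the treatment arm". Difference = 1.85 − 0.9 = 0.95 percentage points.
- Spread and level: "with a standard deviation (SD) of 1.6% and an alpha of 0.05". Sidedness is not stated; two-sided is assumed.
- Evaluable numbers: 80 per arm with 20–30% dropout gives 80 × 0.80 = 64 down to 80 × 0.70 = 56.

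**Step 3: reproduce the plan's own figure**

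The normal approximation is n = 2(1.96 + 0.842)² × 1.6² / 0.95² = 44.5, so 45 per arm. The two-sample t-test version gives 45.5, so 46 per arm, with power 80.4%. The stated 46 per arm for more than 80% power is reproduced.

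**Step 4: dilution**

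Let f be the share of placebo women who take a prebiotic and s the share of the full synbiotic effect they gain. Both are assumptions, because the documents give neither. The expected difference becomes

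Δ = 0.95 × (1 − f × s).

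Two-sample t-test power, SD 1.6, two-sided 0.05:

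| f | s | Δ | 46 per arm | 56 per arm | 64 per arm |
|---|---|---|---|---|---|
| 0 | – | 0.950 | 80.4% | 87.6% | 91.5% |
| 5% | 0.25 | 0.938 | 79.4% | 86.8% | 90.8% |
| 10% | 0.5 | 0.9025 | 76.3% | 84.1% | 88.6% |
| 20% | 0.5 | 0.855 | 71.7% | 80.0% | 85.1% |
| 30% | 0.5 | 0.8075 | 66.8% | 75.4% | 80.9% |
| 20% | 1.0 | 0.760 | 61.6% | 70.2% | 76.0% |

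The last row is an extreme: it supposes that inulin alone delivers everything that five strains plus inulin deliver. Only the product f × s matters, so 10% uptake at full effect gives the same result as 20% at half effect.

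The SD is held at 1.6. Mixing users and non-users in the placebo arm adds variance f(1 − f)(0.95s)². For f = 20% and s = 0.5 that is 0.20 × 0.80 × 0.475² = 0.036, against 1.6² = 2.56, which is negligible.

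**The case against.** The strongest reply is that this sets an abstract against a short section of a condensed article. The detailed criteria are in Figure 4, which is not shown; trial conduct is described in Supplementary File S1; and participants receive a tip sheet. Any of these may word the restriction more widely. That stands as a limit on certainty. It does not remove the point, because the article does state a restriction, and states it more narrowly than its own description of the population.

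A second reply is that women enter as non-users, so starting an inulin supplement arguably departs from the request to keep normal dietary patterns. This gives some cover, but weak cover: it is a request, it names no supplement, and the same section names probiotics and hormone therapy explicitly rather than relying on it.

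A third is that an entry criterion and an in-trial instruction serve different purposes, and nothing in 2.5 positively permits prebiotics. That is fair: this is a gap between two rules, not a logical contradiction.

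Three stronger readings are tempting and should be resisted.

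- A reader might infer that a placebo woman who takes inulin would remain in the per-protocol set. The article does not define that set, and its definition may properly sit in the analysis plan, so this cannot be said.
- A reader might infer that such use would go unseen. Current Medications is recorded at every visit, and diet and stool measures are also collected. Whether supplements are itemised is not shown, but invisibility is not established. What the record does not do is settle whether the use is a deviation.
- A reader might infer that extra prebiotic use in the active arm also biases toward zero. If inulin is beneficial, such use would leave the difference unchanged or enlarge it. Uptake in both arms could partly offset. Only placebo-arm use dilutes the contrast in the way calculated here.

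**Conclusion.** The mismatch is real and worth correcting; its likely effect on the primary result is modest. As written, prebiotics matter at entry but are not named in the in-trial supplement restriction, and the resulting placebo-arm exposure would bias toward no difference.

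With half the effect assumed for inulin alone, 10% to 20% uptake costs roughly 3 to 8 points of power at 56 to 64 evaluable per arm and leaves it at about 80% or above. Power falls clearly below 80% only with fairly common uptake or a large inulin-only effect, because the sample has slack: 46 evaluable per arm are needed and 56 to 64 are expected.

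This rests on the 2.8 planning values, a two-sided test, uptake confined to the placebo arm, and assumed values for uptake and the inulin-only effect. It does not threaten the trial's validity, and it supports no conclusion about who would be in the per-protocol set.

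**What to change.** - Reconcile the abstract's entry description with 2.5 so that the same class of products is covered at entry and throughout follow-up. If Supplementary File S1 or the full protocol already does this, align the article's wording with it.
- Capture prebiotic supplement use as a specific item on the Current Medications record already scheduled in Table 1.
- Before unblinding, state whether such use is a protocol deviation and how it is handled in the per-protocol analysis. Report its frequency by arm, so that dilution can be judged from data rather than assumed.

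The cost is one line in the participant instructions, one item on an existing form, and one sentence in the analysis rules. Design, sample size and endpoint are unchanged. The article reports that the trial is under way, so the instruction can reach only the remaining follow-up; earlier use can be reviewed from the medication records while the data are still blinded.

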### 2.6. Visit Windows

The T0 visit date will set the follow-up visit dates, which will be booked one week on either side of the designated visit date unless there are extenuating circumstances (for example, unavailable due to illness). Any visit/contact that occurs outside one week on either side of the visit windows will be recorded in REDCap as a protocol deviation for that visit. Visits requiring blood sampling and stool collections will be conducted six months apart at T0, T2, and T4, with an additional stool collection at the final visit. Additionally, participants will be given a 72-h window in which to collect the stool samples and all materials required for the collection. Visits requiring fasted blood collection will be scheduled early in the morning and at a time convenient for study participants. The screen and T4 visits, which include DXA and HR-pQCT scans, will take no longer than 3 h to complete. Participants will be provided with breaks, food, and drinks at all in-person visits, as needed. To ensure adherence, participants will be sent email reminders of what a visit entails a week prior to each visit and contacted the day before the visit via telephone, where requirements for the visit will be discussed again.

### 2.7. Outcomes

#### 2.7.1. Primary Outcome

High-resolution peripheral quantitative computed tomography (HR-pQCT) scans will be performed to assess total BMD (BMD) and bone microstructure at the nondominant distal radius and distal tibia. Scans will be obtained at the standard ultradistal site and 30% of the bone length of the tibia and radius sites (XtremeCT II, Scanco Medical AG, Brüttisellen, Switzerland) with a protocol described earlier [72]. Once images are processed, the following parameters are obtained: total BMD (mg/cm^3^), cortical cross-sectional area (mm^2^), cortical BMD (mg/cm^3^), and the trabecular bone volume fraction (%). The muscle area, density, intramuscular fat and subcutaneous fat, at the distal tibia will also be measured via HR-pQCT. The CVs for the HR-pQCT bone measurements in our facility range from 0.29% to 3.61% for the tibia bone measurements.

#### 2.7.2. Secondary Outcomes

##### Dual-Energy X-Ray Absorptiometry (DXA)

Areal bone mineral density (aBMD, g/cm^2^) will be measured at the lumbar spine (L1–L4) and proximal femur (total hip and femoral neck) as well as the full body composition (fat and lean mass) via Lunar iDXA, a GE HealthCare machine with Lunar iDXA enCORE Bone & Metabolic Health software version 18 (GE HealthCare, Buckinghamshire, UK). Standardized procedures for participant positioning and scan analysis will be used [73]. Follow-up measurements will be evaluated via the ‘comparison’ feature of the Lunar iDXA enCORE Bone & Metabolic Health software Version 18. DXA is widely recognized as the gold standard for evaluating BMD and is routinely used for diagnosing both primary and secondary osteoporosis [73]. DXA derived BMD data will be used as part of both the exclusion criteria and outcome measures (secondary) at screening and T4 visits, respectively. The percentage coefficient of variation (CV) for scans repeated on 30 participants in our facility is 0.63% for the lumbar spine, 1.18% for the femoral neck aBMD, and 0.69% for the whole-body BMD.

##### Continuous Glucose Monitoring (CGM)

The participants will be fitted with the minimally invasive Freestyle Libre Pro IQ CGM at the screen, T2 and T4 visits per the manufacturer’s instructions [74], and they will wear the device for a duration of 10 days. This system, a commercially available factory-calibrated sensor, is waterproof and is inserted rather painlessly into the subcutaneous tissue over the triceps. This device measures interstitial glucose continuously in the range of ≥40 mg/dL to 500 mg/dL [74]. By measuring interstitial glucose every 5–15 min, the device provides a comprehensive 24-h glycemic profile, with enhanced assessment of nocturnal and/or asymptomatic hypoglycemia and pattern recognition during the treatment period.

##### Physical Activity Monitoring

To assess habitual physical activity and sedentary behavior, participants will be fitted with a triaxial ActiGraph GT3x accelerometer (ActiGraph, Pensacola, FL, USA) worn at the hip (Figure S3). Before the visit, the accelerometer will be initialized by research staff to record data at a sampling frequency of 30 Hz in three axes: vertical, mediolateral, and anteroposterior, using ActiLife software (V6.13.4 Lite Edition, ActiGraph, FL, USA). The device will be fitted at screen, T2, and T4, and worn for a 10-day period. The data will be downloaded and aggregated into 1-min epochs via ActiLife software (V6.13.4 Lite Edition, ActiGraph, FL, USA). At these visits, participants will also receive a diary to record the times they wear an accelerometer, their sleep and wake times and their physical activity levels (Figure S4). The participants will be encouraged to maintain their normal daily routines during this period.

##### Trial Questionnaires

The questionnaires, either self-reported or obtained in a semi-interview with the trial participants, will be administered via and recorded in REDCap. Table 1 shows an overview of the trial questionnaires and the associated timepoints for data collection. Two in-house self-report questionnaires will be administered. Specifically, dietary patterns of fermented food intake will be measured via an exploratory self-reported fermented food frequency questionnaire and an exit survey, both of which are administered via REDCap (Supplementary File S4).

##### Blood Biomarker Measurements

There will be three venous fasting blood collection timepoints (T0, T2, and T4) and three finger prick blood draws (screening, T2, and T4). Blood samples will be collected from the cubital vein by a qualified venipuncturist at a hospital pathology contracted by the researchers.

At T0, T2, and T4, blood samples will be tested for fasting blood glucose and insulin by the hospital’s pathology laboratory staff via a commercial enzymatic kit (Beckman Coulter Inc., Brea, CA, USA) with a CV of 1.6–2.6% and a chemiluminescent microparticle immunoassay Architect Insulin 8K41 kit (Abbott GmbH & Co., Wiesbaden, Germany) with a precision of ≤7% total CV. The remaining serum and plasma will be aliquoted and stored in a −80 °C freezer for further analysis. At the completion of the trial, these samples will be analyzed via commercially available immunosorbent assays for the following bone turnover markers: C-terminal cross-linking telopeptide of type I collagen, procollagen type 1 N-terminal propeptide, high-sensitivity C-reactive protein and osteocalcin at T0, T2, and T4. A flowchart of the blood collection and processing procedure is illustrated in Figure S5.

Furthermore, the first 80 randomized participants will undergo an additional blood analysis of the number of circulating regulatory T cells (Tregs) (n = 40 per arm). Blood for this analysis will be collected at T0 and T4, and this collection will not require an additional blood draw. Tubes will be spun by pathology staff before being sent by a courier to a collaborator for peripheral blood mononuclear cell isolation and storage in liquid nitrogen until completion of the trial [91]. Treg analysis will be subcontracted to an external facility at the completion of the trial.

##### CogState Brief Battery

Cognitive performance will be measured via the CogState brief battery for outcome purposes at screen (practice), T0, T2, and T4 [92]. Practice will assist in controlling the learning effect associated with the assessment. CogState has been specifically designed to detect changes in cognitive performance from repeated measures in a clinical trial setting. This tool demonstrates good acceptability, efficiency, and stability and minimizes practice effects. The test battery will include the Groton maze learning test (executive function test), the continuous paired associate learning test (spatial paired associative learning test), the one back test (working memory test), and the social-emotional cognition test (emotional recognition) [93,94,95]. The total administration time will be approximately 24 min.

